#### **M. Selection of comparison group(s) or controls**

For objectives 1 and 2 the comparison group consists of the patients prescribed warfarin with a diagnosis of AF meeting the eligibility conditions described in section L. For objective 3 apixaban is compared to each other treatment group (warfarin, rivaroxaban, dabigatran).

#### **N. Exposures, Outcomes and Covariates**

The exposures of interest are apixaban, warfarin, rivaroxaban, and dabigatran (any dose for each exposure).

The individual effectiveness outcomes:

- stroke
- systemic embolism
- myocardial infarction
- all cause death

The safety outcome for the study:

- major bleeding (bleeding requiring transfusion, bleeding at a critical site, bleeding requiring attendance at hospital, or fatal bleeding)

For all outcomes we make the assumption that if there is no record of an outcome then the outcome did not occur.

The EHR ARISTOTLE-eligible patients prescribed apixaban will be matched to the ARISTOTLE apixaban patients on the variables listed in section L (step 3 of objective 1), with value taken at baseline (value at time of first dose or latest measurement/data recorded prior to first dose).

When matching between the treatment arms within the EHR cohort of patients the variables to be considered for inclusion in the matching algorithm include those listed in section L used in matching from the EHR treatment arm to the trial patient data in addition to EHR variables such as data source (CPRD Gold or Aurum), socioeconomic status, and comorbidities.

[figure not shown]

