#### 13. Please select any linked data or data products being requested

##### Patient Level Data (place 'X' in all boxes that apply)

|                                               |   |                                                                                    |  |
|-----------------------------------------------|---|------------------------------------------------------------------------------------|--|
| ONS Death Registration Data                   | X | CPRD Mother Baby Link                                                              |  |
| HES Admitted Patient Care                     | X | Pregnancy Register                                                                 |  |
| HES Outpatient                                |   | NCRAS (National Cancer Registration and Analysis Service) Cancer Registration Data |  |
| HES Accident and Emergency                    |   | NCRAS Cancer Patient Experience Survey (CPES) data                                 |  |
| HES Diagnostic Imaging Dataset                |   | NCRAS Systemic Anti-Cancer Treatment (SACT) data                                   |  |
| HES PROMS (Patient Reported Outcomes Measure) |   | NCRAS National Radiotherapy Dataset (RTDS) data                                    |  |
|                                               |   | Mental Health Services Data Set (MHDS)                                             |  |

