### **Objectives**

**Objective 1.** Check comparability of EHR data and robustness of methods for measuring AF stroke prevention medication effectiveness in EHR data by comparing with ARISTOTLE results.

We will obtain fully anonymised individual patient data from the pivotal ARISTOTLE trial. A group of individuals with similar characteristics will be selected from EHR data based on medical history, prescription data, and baseline characteristics. The ARISTOTLE trial measured the efficacy of apixaban vs warfarin for the prevention of stroke, systemic embolism, myocardial infarction, and mortality and safety (major bleeding) amongst people with AF and at least one risk factor for stroke. Individual trial participants will be matched with similar people in the anonymised EHR databases the Clinical Practice Research Datalink (CPRD) Gold and CPRD Aurum in order to create an ARISTOTLE-analogous cohort within EHRs. The individual trial participant information is being obtained from Bristol Myers-Squibb. Using cohort methodology, estimates of the effect of apixaban vs warfarin on stroke, systemic embolism, myocardial infarction, major bleeding and mortality in the CPRD cohort of ARISTOTLE analogous patients will then be measured. The results will be compared with the ARISTOTLE findings to determine the utility of CPRD records for measuring medication effectiveness in AF. This objective will provide a methodological framework for measuring drug effectiveness in people with AF, using observational data from CPRD.

**Objective 2.** Extension of trial findings: Measure AF treatment effects in patients excluded from ARISTOTLE

Using the methodological template developed in Objective 1, we will determine the effect of apixaban vs warfarin in prevention of stroke, systemic embolism, myocardial infarction, major bleeding and mortality in people with AF not eligible for the ARISTOTLE study (most importantly people with substantial comorbidity), and look separately at important subgroups e.g. those with and without underlying cardiovascular disease.

**Objective 3.** Comparative effectiveness: Compare treatment effectiveness between multiple individual anticoagulants in all anticoagulant recipients (no eligibility criteria other than diagnosis of AF)

Using the methodological template developed in Objective 1, we will compare time to stroke, systemic embolism, myocardial infarction, major bleeding, and death based on prescribed treatments:

- a) warfarin
- b) apixaban

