**K. Planned use of linked data (if applicable):**

We intend to use CPRD data linked with HES in patient data to enable optimal stroke, MI, and major bleeding ascertainment, and ONS mortality data to determine deaths. When matching CPRD patients we plan to include the practice level deprivation level index as a matching variable because socioeconomic status is predicted to influence the likelihood of the primary study outcome of stroke.

[figure not shown]

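### Major bleeding includes any bleed needing hospital attendance, a criterion with no severity floor that the requested hospital data only partly cover

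*Protocol*

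**What the plan says.** Section N of the Protocol gives one safety outcome: "major bleeding (bleeding requiring transfusion, bleeding at a critical site, bleeding requiring attendance at hospital, or fatal bleeding". The same section adds: "For all outcomes we make the assumption that if there is no record of an outcome then the outcome did not occur".

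The patient-level table under item 13 shows which linked data are requested. "HES Admitted Patient Care" and "ONS Death Registration Data" are marked. "HES Accident and Emergency" and "HES Outpatient" are listed but left blank. Section K matches this request: "We intend to use CPRD data linked with HES in patient data to enable optimal stroke, MI, and major bleeding ascertainment".

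Section O (Secondary analyses) names major bleeding as the key safety outcome. It is analysed with the on-treatment censoring scheme and used for all three objectives. Section E (Objective 1) lists major bleeding among the effects to be estimated and then says: "The results will be compared with the ARISTOTLE findings to determine the utility of CPRD records for measuring medication effectiveness in AF".

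**The concern.** Because the criteria are joined by 'or', the least demanding one sets the threshold. Hospital attendance carries no condition on admission, transfusion, site or outcome, so an attended nosebleed ranks with an intracranial haemorrhage.

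The records that would show attendance without admission are also not requested. Such bleeds can be seen only through GP coding, and those not coded become non-events by rule. The outcome would be broad on paper and narrower in practice, by an unknown amount.

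At stake is the only safety outcome in the study. It is set beside the ARISTOTLE bleeding result in Objective 1 and carried into Objectives 2 and 3, where no trial result exists to check it against.

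**Working it through.** The Protocol gives no event rate, hazard ratio or sample size for bleeding, so there is no figure to reproduce. The check sets each part of the definition against the data requested.

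**Step 1. Source for each criterion.**

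| Criterion (section N) | Source available under item 13 and section K |
|---|---|
| Transfusion or critical site | HES admitted-patient data; CPRD if coded |
| Fatal | ONS death registration |
| Hospital attendance, admitted | HES admitted-patient data |
| Hospital attendance, not admitted | CPRD only, if the GP record codes it |

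Only the last row lacks a hospital source.

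**Step 2. What happens to uncaptured events.** Under section N, an attendance that no source records is treated as an event that did not happen. It is not treated as missing.

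**Step 3. What happens to captured events.** Under the supportive censoring scheme in section O, follow-up for an outcome ends when that outcome occurs. A recorded attendance-only bleed therefore ends the patient's time at risk, and a later serious bleed in that patient no longer counts towards the composite.

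**Step 4. Whether other parts of the plan repair this.**
- Section O also summarises bleeding by site. That separates intracranial from gastrointestinal and other bleeds, but does not separate serious from minor bleeds within a site.
- Section Q (Missing Outcome Data) repeats the primary analysis in the linked cohort. The primary analysis is stroke/systemic embolism, so bleeding is not covered.
- Section T discusses vague wording in the bleeding-risk eligibility criterion, not in the bleeding outcome.

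**Step 5. Illustration of size, on assumed inputs only.** Let f be the share of recorded warfarin-arm events that qualify by attendance alone. Then approximately

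observed HR = (1 − f) × HR(serious) + f × HR(attendance-only).

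With HR(attendance-only) = 1.0:

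| f | HR(serious) 0.60 | 0.70 | 0.80 |
|---|---|---|---|
| 0.2 | 0.8 × 0.60 + 0.2 = 0.68 | 0.8 × 0.70 + 0.2 = 0.76 | 0.8 × 0.80 + 0.2 = 0.84 |
| 0.3 | 0.7 × 0.60 + 0.3 = 0.72 | 0.7 × 0.70 + 0.3 = 0.79 | 0.7 × 0.80 + 0.3 = 0.86 |
| 0.5 | 0.5 × 0.60 + 0.5 = 0.80 | 0.5 × 0.70 + 0.5 = 0.85 | 0.5 × 0.80 + 0.5 = 0.90 |

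If GP coding catches almost none of these bleeds, f approaches 0 and the dilution disappears.

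The direction is not fixed either. Suppose attendance-only bleeds were recorded 1.3 times as often on warfarin, with no drug effect. Their apparent HR would be 1/1.3 = 0.77. With HR(serious) = 0.80 and f = 0.5, the observed HR would be 0.5 × 0.80 + 0.5 × 0.77 = 0.785, slightly further from 1 than 0.80. None of these inputs comes from the Protocol.

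**The case against.** The strongest reply is that the two faults offset each other. If attendance-only bleeds are mostly uncaptured, the requested data already confine the outcome to admitted or GP-coded bleeds, which is close to the proposed remedy, and the dilution is small. This stands as a limit on size. It does not remove the problem, because how much GP coding lets in is unknown and the result would still be reported under a definition that the data do not implement.

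The reply also rightly says that bleeding is a secondary outcome. Both consistency criteria in section O concern stroke/systemic embolism, so no success rule turns on bleeding. The intracranial summary would also be largely free of attended minor bleeds.

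Code lists can be left to later documents. The attendance criterion, however, is a stated outcome rule and not a coding detail.

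A reader might infer more than the document supports:
- **That major bleeding cannot be measured.** Admitted bleeds are in the HES data, deaths are in the ONS data, and some attendances will be in CPRD.
- **That the result will not be comparable with ARISTOTLE.** The Protocol does not give the trial's bleeding definition, so a mismatch cannot be shown from it.
- **That cause of death will go unused.** Section K says ONS data will determine deaths, but does not exclude using them to identify fatal bleeding.
- **That recording differs by arm.** Section F describes closer monitoring on warfarin, but says nothing about how GPs code hospital bleeds.

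**Conclusion.** The point holds in a limited form. One of four sufficient criteria for the key safety outcome has no severity threshold and does not match the data request. Attendances without admission enter only through GP coding and otherwise count as no event. The resulting composite has an unknown share of less serious bleeds, so agreement or disagreement with ARISTOTLE on bleeding would be hard to interpret. Comparability is at risk; it is not shown to be lost.

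The size and direction of any bias cannot be derived from the document. The illustrated shift, for example from 0.70 to between 0.76 and 0.85 for f between 0.2 and 0.5, rests wholly on assumed values and on attendance-only bleeds being unaffected by drug. The stroke/systemic embolism validation is untouched. This is an inexpensive change that should be made; it does not undermine the study.

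**What to change.** In section N:
- Replace the hospital-attendance criterion with hospital admission for bleeding, defined as bleeding in the primary diagnosis of a HES admitted-patient record.
- Keep the transfusion, critical-site and fatal criteria, and state that fatal bleeding is identified from the ONS data already requested.
- Report GP-coded or attendance-only bleeds as a separate outcome.
- Use the admission, critical-site, transfusion or fatal definition for the comparison with ARISTOTLE.

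Apply this in the HES- and ONS-linked cohort that section L (Objective 1, Step 1) specifies. Section Q (Missing Outcome Data) treats linkage as a sensitivity analysis, and the two sections need to be reconciled: an unlinked patient could not meet the HES criterion and would be counted as having no event. The linkage restriction is written under Objective 1 only, so the rule for Objectives 2 and 3 should be stated as well.

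If attendance is to stay in the definition, the alternative is to request the HES emergency data. That would improve capture but still leave no severity threshold.

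The preferred change needs only revised wording and a code list on data already requested. The cost is fewer bleeding events and a somewhat wider confidence interval.

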## **O. Data/ Statistical Analysis**

### **Data mapping**

For all 3 objectives the data source will consist of two datasets of UK real world clinical data which will be combined: CPRD Gold and CPRD Aurum. The two datasets will be mapped to a common data model based on adapted Clinical Data Interchange Standards Consortium (CDSIC) standards. Duplicate entries of patients – where a patient is present in more than one dataset – will be removed with the following rule: keep in CPRD Aurum above CPRD Gold. CPRD Aurum provides a dataset listing practices in CPRD Aurum which have previously contributed data to CPRD Gold; this dataset will be used to exclude data from practices with eligible patients in CPRD Gold where the patient data is also recorded in Aurum. Only data of interest to the study will be mapped and used: patient demographics, diagnoses, clinical events, and recorded symptoms, therapies prescribed, lab results, and vital signs.

### **Primary Analysis**

#### **o Population**

The ARISTOTLE trial used an intent to treat (ITT) approach for the primary efficacy analysis, and an on-treatment approach for the sensitivity analyses and safety outcomes. To perform an equivalent analysis with the EHR data the following analysis populations will be used for all objectives:

Prescribed Population: all patients who were prescribed a treatment, regardless of future changes to treatment.

When summarizing data using this population, subjects are categorized according to the As Prescribed group.

On-treatment Population: all patients who were prescribed a treatment. In the case of patients discontinuing or switching treatment, data will be included up to and including their derived date of last dose of the initially prescribed treatment.

#### **o Censoring**

##### Index date

The index date for the EHR cohort will be the date of the patient's first prescription of apixaban or warfarin (for objectives 1 and 2), or for objective 3 first prescription of apixaban, warfarin, rivaroxaban, or dabigatran on or after the date the patient first met the eligibility criteria for the trial in the treatment period of interest

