A patient may be exposed to warfarin followed by apixaban in the time period of interest and the patient be trial eligible in both treatment periods; in such a situation both patient treatment periods may be included in the EHR treatment groups with the restriction that a patient must not be matched to themselves. Given the trial exclusion criteria that a patient may not have been previously exposed to apixaban, any warfarin treatment periods after apixaban exposure would not be eligible for inclusion in the warfarin EHR cohort.

**Objective 2:** we will select patients who would not have been included in the ARISTOTLE trial (and therefore would not have been included in the Objective 1 cohort) based on their age, stroke risk factors, or presence of substantial comorbidity. Specifically, this will be patients with an AF diagnosis in the EHR cohort meeting these additional criteria:

- age >77 years (although elderly patients were not excluded the maximum age at first dose in ARISTOTLE was 76),

OR

- no evidence of at least one additional risk factor for stroke

OR

- AF due to reversible causes

OR

- evidence of drug/alcohol abuse

OR

- severe comorbid condition: ARISTOTLE required patients to be excluded from the trial if they had serious disease with a likelihood of causing death within 1 year or reasons making participation unpractical (such as dementia).

In these special patient populations the same outcomes as objective 1 will be assessed as described in section N.

**Objective 3:** we will select all patients with AF with a prescription for any anticoagulant in the treatment period from the set of treatments: apixaban, warfarin, rivaroxaban, dabigatran. For this objective all outcomes listed in section N will be assessed. Patients will be stratified on whether they would have met the ARISTOTLE trial criteria.

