##### Treatment Switching and Discontinuation

[figure not shown]

As the primary analysis accounts neither for treatment switching nor for treatment discontinuation and does not capture that these may be unfavourable outcomes both the proportion of patients discontinuing treatment and time to treatment discontinuation will be tabulated by prescribed treatment.

o Regression model

Hazard ratio (apixaban/warfarin) comparing the event rate (%/yr).

Interpretation: This estimand targets the treatment-policy effect of treatment initiation of apixaban vs initiation or continuation of warfarin on the time to first stroke or systemic embolism.

All time to event endpoints will be analysed using a Cox proportional hazards model including treatment group as a covariate and prior warfarin/VKA status (experienced, naïve).

Point estimates and two-sided 95% CIs for HR will be constructed for the outcome.

o Validation of Observational Results Against Aristotle Data

In Objective 1 alone we will validate the findings from our primary analysis against ARISTOTLE by determining whether results of the EHR analysis are compatible with the ARISTOTLE trial results. The ARISTOTLE trial demonstrated superiority of apixaban over warfarin for the primary endpoint (HR 0.79, 95% CI 0.66-0.95). The treatment effect seen with the EHR data may be weaker than that seen in ARISTOTLE.

A subgroup analysis looking at the outcomes of the EU patients in ARISTOTLE showed a smaller treatment difference with the estimate for HR below 1 but upper limit of the CI crossing 1 for the primary efficacy endpoint and death: HR for stroke/SE = 0.92 (95% CI = 0.56; 1.52), HR for all cause death = 0.89 (95% CI = 0.68; 1.18). It was suggested in the European Medicines Agency (EMA) Assessment Report that the smaller treatment effect seen in the EU patients could be due to better INR control in the warfarin arm of the EU subgroup (median TTR 68.93%). This study could provide additional evidence on this point. Since all the patients in our cohort are from the UK the results can be compared with the results from the ARISTOTLE patients in the EU.

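### Read literally, the index-date rule gives each patient one start date, which conflicts with the rules letting a patient enter both arms and leaves switchers in Objective 3 unresolved

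*Protocol*

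**What the plan says.** The rule in Section O (Censoring, Index date) is a single sentence. It opens: "The index date for the EHR cohort will be the date of the patient's first prescription of apixaban or warfarin (for objectives 1 and 2". For Objective 3 it substitutes the "first prescription of apixaban, warfarin, rivaroxaban, or dabigatran on or after the date the patient first met the eligibility criteria", and it ends "for the trial in the treatment period of interest".

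Section L describes cohorts built from more than one period per patient:

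- Objective 1, Step 2 lets a person with several warfarin eligibility periods enter the warfarin pool several times, each with its own covariates and person-time, provided there was no earlier apixaban.
- The end of the Objective 1 text considers someone who takes warfarin and then apixaban and is eligible during both. It says "in such a situation both patient treatment periods may be included in the EHR treatment groups", provided the person is not matched to themselves.

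Section L gives no equivalent statement for Objective 3. Section E links that objective to the first: "Using the methodological template developed in Objective 1, we will compare time to stroke, systemic embolism, myocardial infarction, major bleeding, and death". Section O (Regression model) describes the estimand as the "treatment-policy effect of treatment initiation of apixaban vs initiation or continuation of warfarin", with earlier VKA use as a two-level covariate.

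**The concern.** The index date fixes the arm, the baseline covariates used for matching and the start of follow-up. One date per patient, taken at the first of several drugs, cannot produce the two-arm and repeat entries that Section L describes. Two programmers working from this text could build different cohorts.

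Objective 3 is the most exposed, because Section O gives it an explicit first-of-four-drugs rule and Section L gives it no switcher rule. Applied as written, most patients who move directly from warfarin to a DOAC would not appear in a DOAC arm, while continuing warfarin users would stay in the comparator. A two-level covariate for earlier VKA use cannot restore the missing group. The apixaban-warfarin comparison would then not be the contrast that Objective 1 is meant to validate.

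**Working it through.** **1. The literal rule on example histories.** Take the earliest listed prescription on or after the later of 1 January 2013 (start of the window, Section L) and first eligibility. Patients are eligible throughout unless stated.

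| History | Index under the literal rule | Earlier VKA use at index |
|---|---|---|
| (a) Warfarin 2014, apixaban 2016 | Warfarin 2014; no apixaban index | No |
| (b) Warfarin stopped 2010, apixaban 2016 | Apixaban 2016 | Yes, after a gap |
| (c) Last warfarin December 2012, apixaban January 2013 | Apixaban January 2013 | Yes, direct switch |
| (d) Warfarin 2014, eligible only from 2015, no warfarin after that, apixaban 2016 | Apixaban 2016 | Yes |
| (e) Continuous warfarin since 2008 | Warfarin 2013 | Yes |

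Case (a) is the patient whom Section L admits to both Objective 1 groups; the literal rule admits this patient to one. Repeat warfarin entries fail for the same reason. Cases (b) and (e) show how, under the literal rule, a VKA-experienced DOAC patient can be a restarter while the VKA-experienced warfarin patient is an uninterrupted user. Cases (c) and (d) show that this is not universal.

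**2. Does the closing qualifier resolve it?** The Objective 1 switcher text, beginning "A patient may be exposed to warfarin followed by apixaban in the time period of interest and the patient be trial eligible in both treatment", goes on to use treatment periods in the plural for spells on each drug. The Objective 3 paragraph of Section L uses the term, in effect, for the calendar window. In the drug-specific sense Objective 1 is consistent; in the calendar sense it is not. The term is not defined.

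**3. Eligibility in the same sentence.** The clause refers to criteria for the trial. Objective 2 selects patients outside the trial population, some of whom (for example, those with no additional stroke risk factor) need never meet those criteria. Section E says Objective 3 requires only an AF diagnosis. Read as applying to all objectives, the clause leaves some of these patients without an index date. Read as applying to Objective 3 alone, it contradicts that objective's entry rule.

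**4. Size, conditional on the literal rule governing Objective 1.** First, the plan's own figure (Sections I and J):

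- Aurum: 0.60 × 23,526 = 14,115.6, stated as 14,115.
- Gold: 8,407.
- Total: 14,115 + 8,407 = 22,522, which agrees with the stated figure of more than 22,000.

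Let x be the share of these patients with an earlier eligible warfarin prescription in the window. The protocol does not give x, so the values below are assumptions. Remaining pool = 22,522 × (1 − x).

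| x | Pool |
|---|---|
| 10% | 20,270 |
| 20% | 18,018 |
| 30% | 15,765 |
| 40% | 13,513 |
| 50% | 11,261 |

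The stated minimum of 15,000 is breached when x > 1 − 15,000/22,522 = 33.4%. If both periods are admitted, the pool stays at 22,522. No corresponding figure can be derived for Objective 3 or for any hazard ratio.

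**The case against.** The strongest reply is that per-period indexing is plainly intended. Section L gives covariates and person-time to each eligibility period, matches on characteristics at the start of that period, and admits both periods of a switcher. Section I counts apixaban and warfarin patients separately and mentions no removal for earlier warfarin. If the qualifier is read as drug-specific, Objective 1 has no conflict, and Section E's reference to the Objective 1 template may carry the same rule into Objective 3. This stands as evidence of intent. It does not repair a start-of-follow-up rule that says something else, in patient-level wording and with a term used in two senses.

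Several stronger inferences are not supported:

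- **Every warfarin-then-DOAC patient is assigned to warfarin.** Case (d) shows otherwise: warfarin before first eligibility does not set the index date.
- **VKA-experienced DOAC patients would all be restarters.** Case (c) is a direct switcher, and users of VKAs other than warfarin, which are not listed exposures, also fall in this group.
- **Continuing warfarin users are misplaced.** The estimand puts them in the comparator by design.
- **The index rule causes DOAC time to count as warfarin time.** That follows from the primary censoring scheme, which does not censor at switching, and it would remain after the index date is corrected. The protocol acknowledges switching and plans an on-treatment analysis.
- **The pool shrinkage is a prediction.** The minimum of 15,000 belongs to Objective 1, where Section L expressly admits switchers.

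**Conclusion.** The point holds as a conflict between the stated index-date rule and the cohort rules in Section L. Followed literally, the rule gives an eligible patient with warfarin and then apixaban in the window no apixaban index date, and it cannot support repeat warfarin entries. The qualifier does not resolve this. Separately, the sentence ties Objectives 2 and 3 to trial eligibility that their own entry criteria do not require.

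The consequence for Objective 3 is an inference. It needs both the literal reading and the assumption that the Objective 1 multiple-period rule does not carry over. On those terms most direct switchers are missing from the DOAC arms, and the contrast differs from the validated one by an amount the protocol does not allow one to compute. The 33.4% threshold rests on the literal reading being applied to Objective 1 and on an assumed share of switchers. The rule should be corrected before cohorts are extracted, because a later change means rebuilding and rematching them.

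**What to change.** Rewrite the index-date paragraph as follows:

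- Define the index date per arm and per eligibility period: the first prescription of the drug defining the arm within each period in which that objective's own entry criteria are met.
- Keep the repeat warfarin periods of Section L, Step 2, and Objective 1's restriction to patients with no earlier apixaban. One warfarin index per patient would create a new conflict with Step 2.
- State that the multiple-period rule, including the bar on self-matching, applies to Objectives 2 and 3.
- Define treatment period once and use it in that sense throughout.
- Use robust standard errors clustered by patient wherever one person contributes more than one record.

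The cost is protocol wording, one change to the cohort-building program, and correlated records that the clustered standard errors handle.
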